### Data collection

To minimise interruptions caused by COVID-19 lockdowns, data collection is designed to involve minimal face-to-face contact. Demographic data (including age, sex, ethnicity, postcode, medications, nominated General Practitioner or case manager) are obtained via phone interview upon enrolment. At both baseline and 8-week follow-up, the blinded research assistant administers a battery of questionnaires via a Computer-Assisted Telephone Interview (CATI). This CATI takes approximately 30-60 min to complete and is conducted by a research assistant with specialised training. In addition to the CATI, the Mini-International Neuropsychiatric Interview (MINI) is administered in a separate Zoom call by a trained Clinical Psychologist or Provisional Psychologist. The MINI is a structured diagnostic interview designed to assess 17 of the most common mental health disorders [30]. It is used here to examine the prevalence of current and past major psychiatric disorders in the trial population.

In the absence of any COVID-19 related lockdown, consenting participants are also invited to complete an in-person visit at Australian Clinical Labs Collection Centre and Health Education and Research Building (both in Geelong). This visit cannot be administered via telephone. It includes a fasting blood test; weight, height, waist and hip measurements; blood pressure assessments; and muscular strength tests. Stool samples are provided by participants and returned via the post and stored in laboratory facilities at the Research Centre. As research assistants conducting data collection are blinded to participants’ program allocation, prior to the 8-week follow-up assessments participants are reminded not to reveal the group they have been assigned to in order for research assistants to retain blinded status.

If a participant chooses to withdraw from the study or is withdrawn by the research team (due to an adverse event, violating inclusion criteria, or if continuing would be detrimental to their wellbeing), data collected up until that time point will be used in the analysis of results, unless otherwise requested by the participant. A research assistant will also make a reasonable attempt to collect the primary outcome from withdrawing participants by organising a follow-up CATI.

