#### Intervention adherence and integrity

Participants’ attendance at each of the intervention sessions are recorded by the facilitators. Completion of the intervention is categorised as 50% or greater exposure/attendance (i.e. 3 or more sessions). At the conclusion of each telehealth session, the facilitators present five questions with Likert-style response options to participants to obtain session feedback. The results of these polls are used to guide the structure of future sessions to enhance participant engagement. All sessions are recorded on Zoom unless a participant does not consent to the recording. Approximately 10% of session recordings are assessed independently by two research staff to determine fidelity to both the CALM and psychotherapy conditions.

For participants in the CALM intervention arm only, the Mod*i*Med Diet Weekly Checklist [51] is used to assess how fully participants are engaging in a modified Mediterranean diet, as promoted by the CALM intervention. Engagement in the CALM physical activity objectives is monitored continually throughout the intervention period via the active minutes output obtained from FitBits that are provided to participants allocated to the CALM ‘lifestyle’ program at trial commencement. They are also asked to complete two items from the SIMPAQ and Borg scale to capture physical activity intensity on a weekly basis.

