To encourage engagement with healthful dietary habits, participants are sent a food hamper at completion of their first session, which contains the key components of the Mod*i*Med diet to inspire and promote dietary change. This strategy has previously been used to successfully promote engagement in RCTs of other Mediterranean-type dietary approaches [7, 61]. For the physical activity sessions, participants are provided with a resistance band as a convenient, portable, and effective alternative to free weights and weight machines. They are also sent a FitBit Charge 2 to self-monitor their physical activity (pedometer). Participants are also encouraged to complete a Mod*i*Med checklist, a physical activity tracker and utilise health apps, to increase their engagement and build on skills learnt throughout the sessions.

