#### Psychotherapy program

Cognitive Behavioural Therapy is widely recommended as a gold-standard psychological intervention for multiple mental health presentations [4, 62, 63], and has demonstrated effectiveness when delivered in groups (e.g., [64, 65]) and via telehealth (e.g., [66, 67]).

The psychotherapy program is a transdiagnostic CBT group adapted from the manualised Mood Management Course that was developed by the Centre for Clinical Interventions (CCI) [68]. The psychotherapy program also incorporates mindfulness practices, with a growing body of research suggesting that the integration of mindfulness and CBT can improve clinical outcomes [69, 70].

CBT proposes that the cognitive and behavioural factors which maintain mental health distress are amenable to change through recognising and challenging these unhelpful patterns [71]. As such, the psychotherapy group aims to develop skills in self-awareness, identifying and managing unhelpful thoughts and behaviours, and learning and practicing self-management strategies. Each session includes guided mindfulness practice. Each group is facilitated by a clinical or registered psychologist and a provisional psychologist.

To ensure parity with the CALM ‘lifestyle’ program, participants are sent a self-soothe hamper at commencement of the program, which includes items such as a colouring book, head massager, and stress ball. Participants are also encouraged to utilise mental health apps, to increase their engagement with skills such as mindfulness, breathing, thought logs, and cognitive disputation.

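### Assessor blinding at the optional 8-week in-person visit is not protected against a FitBit issued only to the CALM arm (minor; strength counts and waist/hip only)

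*Protocol article*

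**What the plan says.** All references are to the protocol article.

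- **Blinding and its safeguard.** The Data collection section describes the research assistants as blinded to allocation. Before the 8-week follow-up, "participants are reminded not to reveal the group they have been assigned to in order for research assistants to retain blinded status". No other step to keep them blinded at that visit is stated.
- **The device.** Intervention adherence and integrity says that CALM physical activity "is monitored continually throughout the intervention period" through the "active minutes output obtained from FitBits that are provided to participants allocated to the CALM" program. The 'CALM' lifestyle program section names the model, a FitBit Charge 2, and describes it as a pedometer for self-monitoring.
- **The other arm.** Psychotherapy program says that, for parity, "participants are sent a self-soothe hamper at commencement of the program". The examples of its contents include no wearable.
- **The visit.** Outside lockdown, consenting participants are invited to attend in person. On content, Data collection says: "It includes a fasting blood test; weight, height, waist and hip measurements; blood pressure assessments; and muscular strength tests". Table 1 lists the strength tests as 30-second sit-to-stand and bicep-curl tests, and says blood pressure is taken with an automatic device.
- **The primary outcome.** The PHQ-9 is part of a telephone interview and is asked first.

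**The concern.** The safeguard relies on what participants disclose, but the trial itself gives one arm an object that can disclose the allocation for them. The device is in use until the program ends, which is also when the follow-up assessment takes place. At the visit the assistant is face to face with the participant, watching arm curls and placing a tape measure.

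Repetition counts can shift with encouragement and with how a borderline repetition is scored. Circumferences can shift with tape placement. CALM promotes physical activity and supplies a resistance band, so an assistant who recognises a CALM participant may expect better strength results. At stake is the credibility of the blinded label for a small set of secondary outcomes.

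**Working it through.** The plan gives no figure on this point, so the check is mainly a comparison of sections.

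**Step 1: is there an arm-specific cue?** Yes, in the listed supplies. CALM receives a FitBit; the psychotherapy hamper is described without a wearable.

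**Step 2: could it be present at the visit?** Plausibly. Monitoring runs through the intervention period, and Study design places the follow-up at program completion (8 weeks). Wear at the visit is still an inference. The text does not say where on the body the device is worn, or whether it is still in use on the day. A psychotherapy participant could also own a tracker.

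**Step 3: does the stated safeguard deal with it?** Not explicitly. The reminder concerns revealing the group, and no instruction about the device is attached to it.

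**Step 4: which outcomes are exposed?**

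| Outcome | How obtained | Open to assessor influence from seeing a device? |
|---|---|---|
| Sit-to-stand, bicep-curl counts | In person, effort-dependent | Yes |
| Waist, hip | In person, measured by hand | Yes |
| Weight, height | In person | Little |
| Blood pressure | In person, automatic device | Little |
| Fasting bloods | Analysed by an outside laboratory | No |
| PHQ-9 and other interview scales | Telephone | Device cannot be seen |

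That research assistants take the in-person measurements is read from the paragraph that describes the visit and then their blinding. The article does not assign each measurement to a named role.

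**Step 5: an illustration of scale, on assumed inputs only.** The documents give neither an SD nor an attendance figure for the exposed outcomes. Let b be the average assessor bias across the CALM arm in SD units, and n the number measured per arm. For a two-sided 5% z-test that ignores clustering, the non-centrality is b × √(n/2), and the false-positive rate is 1 − Φ(1.96 − b√(n/2)) + Φ(−1.96 − b√(n/2)).

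| Assumed b | n = 40 per arm (assumed attendance) | n = 80 per arm (full analysed sample in Sample size) |
|---|---|---|
| 0 | 5.0% | 5.0% |
| 0.1 SD | 7.3% | 9.7% |
| 0.2 SD | 14.5% | 24.4% |
| 0.3 SD | 26.9% | 47.5% |

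Worked entry: b = 0.1 and n = 40 give 0.1 × √20 = 0.447, and a rate of 7.3%. Because b is an average over the arm, it is diluted when few participants are identifiable. If half were, and each was scored 0.2 SD too high, b = 0.5 × 0.2 = 0.1. The table shows only that a small systematic shift would matter for these outcomes. It is not evidence that a shift occurs.

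**The case against.** **The reminder is broader than speech.** Asking participants not to reveal their group could be taken to cover showing a trial-issued device. That is fair. But nothing stated tells participants that the device counts, and one worn out of habit is easily overlooked.

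**The article is condensed.** Appointment instructions and test scripts often sit in a full protocol or manual. This stands as a limit: the point is that the safeguard stated here does not address the cue the trial creates, not that no such step exists anywhere.

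**The visit is limited.** It is by invitation, needs consent and is held only outside lockdown. This stands and keeps the severity low. A reader might apply a guessed wear rate to the 92 participants per arm (184/2) and quote a number unblinded. The documents support no wear rate, and 92 is a ceiling for an optional visit.

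**The primary outcome.** A reader might infer that an assistant unblinded at the visit then takes the PHQ-9 or GAD-7 by telephone. The documents do not support that. No section says that the same assistant makes both contacts. The order of contacts belongs to Table 2, which is not reproduced in the text available, so it cannot be called missing. The PHQ-9 also has fixed response options, and participants follow it on a paper copy.

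**Direction.** Bias towards CALM is plausible, but nothing in the documents shows it.

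**Conclusion.** The point holds in a narrow form and is minor. As written, the plan calls its assessors blinded, gives one arm a device that can be seen, and states a safeguard that does not mention it. The possible effect is confined to the two strength counts and waist and hip circumference at the in-person visit. It does not touch the non-inferiority conclusion on the PHQ-9.

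This rests on three assumptions: that some CALM participants wear the device visibly to the visit, that research assistants take these measurements, and that no further device instruction exists in documents not shown. The size and direction of any bias are unknown.

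**What to change.** In Data collection, extend the 8-week reminder so that all participants, in both arms, remove wrist and other activity devices before the in-person visit. Addressing both arms matters, because an instruction given only to CALM would itself be a cue and would leave privately owned trackers in view.

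Add one field in which the assistant records after the visit whether the allocation became known. Report it by arm, descriptively only. Do not repeat the comparisons without the participants recorded as unblinded. Those would be mostly CALM participants still wearing the device, who are probably the more adherent ones, so leaving them out would select on a post-randomisation, arm-specific marker and break the randomised comparison.

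The cost is one reminder sentence, one form field and a short gap in the device data on the day of the visit. The step can be adopted for any visits still to come.

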#### Outcome measures

A summary of outcome measures and variables are displayed in Table 1. Schedule of enrolment, interventions and assessments are displayed in Table 2. The 9-item Patient Health Questionnaire-9 (PHQ-9) is the primary outcome of the study and is used to measure depressive symptoms. The PHQ-9 is based on the nine DSM-IV criteria for major depressive episode and is a frequently used clinical and research as a measure of depressive symptoms [27]. It assesses the proportion of days in the past 2 weeks that the respondent experienced various depressive symptoms on a 4-point scale from “Not at all” (0) to “Nearly every day” [3]. Scores range from 0 to 27. A cut-point of > 10 has been identified as providing an important threshold for identifying Diagnostic and Statistical Manual of Mental Disorders (DSM-IV) congruent major depression and shows good sensitivity and specificity [27] (Note: the current version DSM-V has consistent diagnostic criteria to DSM-IV). Of note, a different outcome measure was used to select the sample (i.e., the DQ5) to reduce regression to the mean, which can inflate effect sizes [31].

**Table 1 Tab1:** Summary of assessments

Primary Outcome	Assessment
Depressive symptoms	9-item Patient Health Questionnaire-9 (PHQ-9) [27]
Secondary Outcomes	
Anxiety symptoms	7-item Generalised Anxiety Disorder scale (GAD-7) [32]
Anxiety concerning the COVID-19 pandemic	5-item Coronavirus Anxiety Scale (CAS) [33]
Non-specific psychological distress*	10-item Kessler-10 (K-10) [34]
Perceived social support	4-item (abbreviated) Medical Outcome Study Social Support Survey (MOS-SSS) [35]
Substance use	8-item Alcohol, Smoking and Substance Involvement Screening Test (ASSIST) [36]
Sleep hygiene	7-item Insomnia Severity Index (ISI) [37]
Health-related quality of life	12-item Assessment of Quality of Life (AQoL 4D) [38]
Health service use	Self reported use of prescription and over the counter medications, health professional visits, hospitalisations, absenteeism and presenteeism over the past 8 weeks
Stool consistency	4-item (modified) Bristol Stool Form Scale (BSFS) [39]
Psychosis symptoms	7-item Early Psychosis Questionnaire [40]
Physical activity levels	5-item Simple Physical Activity Questionnaire (SIMPAQ) [41, 42] and a modified Borg scale [43]
IBS diagnosis	1-item self-developed question asks participants if they have been told they have irritable bowel syndrome (IBS) by a general practitioner or gastroenterologist
High-density lipoprotein, Lower-density lipoprotein, total cholesterol	Fasting blood samples
Triglycerides, blood glucose	Fasting blood samples
Cardiovascular health	Systolic and diastolic blood pressure measured using an automatic sphygmomanometer
Waist circumference, hip circumference, height, weight	Height (to the nearest 0.1 cm), body weight (to the nearest 0.1 kg), waist circumference (to the nearest 0.1 cm) and hip circumference (to the nearest 0.1 cm)
Lower body muscular strength and upper body muscular strength	30-s sit-to-stand and 30-s bicep curl test
Diet intake	Dietary Questionnaire for Epidemiological Studies version 3.2 (DQES v3.2)—a modified version of the food frequency questionnaire developed by Cancer Council Victoria [44]
Gut microbiome composition	Stool collection (OMNIgene kits) [45]
Effect modifiers	
Health-related social needs	15-item American Academy of Family Physicians’ Social Needs Screening Tool [46]
Medication adherence	8-item Morisky Medication Adherence Scale (MMAS) [47]
Perceived self-efficacy	6-item (abbreviated) General Self-Efficacy Scale (GSE) [48]
Readiness to make changes in behaviour prior to the intervention [49]	3-item Readiness to Change Questionnaire (RCQ)
Treatment expectancy and rationale credibility	6-item Credibility/Expectancy Questionnaire (CEQ) [50]
Prevalence of current and past major psychiatric disorder	Mini-International Neuropsychiatric Interview (MINI) [30]

*K-10 is also used as a safety measure

**Table 2 Tab2:**
[figure not shown]
Schedule of enrolment, interventions and assessments

The secondary outcome measures were chosen as they assess various relevant aspects of mood including stress, anxiety, depression and health-related quality of life. These questionnaires assessed mood across various time periods (past week to past month). Administration via CATI was chosen to reduce burden on participants. They are also given a paper copy of the questionnaires to follow along. If too burdensome, participants have the option of completing the CATI over two separate calls, or alternatively complete as much as they can. The CATI is structured in order of importance of outcome measures (primary outcome first) to reduce missing data for the primary outcome and ensure retention of participants.

#### Safety

Procedural safeguards are in place for participants exhibiting deterioration in mental health, such as signs of suicidality, sub-optimal medication taking, an adverse event or elevation in psychological distress. Participants complete a fortnightly adverse events questionnaire, which is overseen by the study coordinator and medical personnel. In addition to being administered pre- and post-intervention, the K-10 is also administered each week during the intervention period to assess participant’s levels of generalised psychological distress. The K-10 consists of 10 items to measure non-specific psychological distress [34] and is commonly used in clinical and epidemiological contexts. Scores range from 10 to 50, with higher scores indicating more severe psychological distress. The K-10 is used to examine whether the interventions are having a positive effect on psychological distress throughout the course of treatment. An increase by more than 0.5 standard deviations, or a K10 score increase above 30, between sessions initiates safety protocol procedures.

An independent Data Safety Monitoring Board (DSMB) is overseeing the trial to maximise participant safety and identify patterns in adverse events that may be related to either program. The DSMB consists of members who collectively have experience in the lifestyle based interventions, digital interventions, biostatistics, and randomised clinical trials.

#### Intervention adherence and integrity

Participants’ attendance at each of the intervention sessions are recorded by the facilitators. Completion of the intervention is categorised as 50% or greater exposure/attendance (i.e. 3 or more sessions). At the conclusion of each telehealth session, the facilitators present five questions with Likert-style response options to participants to obtain session feedback. The results of these polls are used to guide the structure of future sessions to enhance participant engagement. All sessions are recorded on Zoom unless a participant does not consent to the recording. Approximately 10% of session recordings are assessed independently by two research staff to determine fidelity to both the CALM and psychotherapy conditions.

For participants in the CALM intervention arm only, the Mod*i*Med Diet Weekly Checklist [51] is used to assess how fully participants are engaging in a modified Mediterranean diet, as promoted by the CALM intervention. Engagement in the CALM physical activity objectives is monitored continually throughout the intervention period via the active minutes output obtained from FitBits that are provided to participants allocated to the CALM ‘lifestyle’ program at trial commencement. They are also asked to complete two items from the SIMPAQ and Borg scale to capture physical activity intensity on a weekly basis.

### Study conditions

All group-based telehealth sessions are delivered using the Zoom for Education platform; a secure, reliable, encrypted video conferencing facility. This platform allows multiple individuals to access a meeting via a computer, tablet or smartphone. Sessions are scheduled to be 90 min, with the option of a 15-min ‘drop-in’ before and after each session.

#### ‘CALM’ lifestyle program

The CALM lifestyle program has been developed by Accredited Practising Dietitians (APD) and Accredited Exercise Physiologists (EP), with the overarching goal to support positive lifestyle changes for mental health. CALM content is derived from the Mod*i*Med Diet used in the SMILES trial [7, 51], the Finnish Diabetes Prevention Study (DPS) [52], the GOAL Program [53], and the Australian Greater Green Triangle Diabetes Prevention Project (GGT DPP) [54]. These studies have all demonstrated successes in achieving improvements in physical and/or mental health outcomes, and hence were considered ideal models in which to develop CALM. The study goals were modified and refined from the original diabetes prevention programs based on the most-up-to date evidence in Lifestyle Psychiatry [6, 10, 55]. Thus, the goals of the CALM program are for participants to achieve:No more than 10% of energy from saturated fats,At least 15 g/1000 kcal fibre (approx. 30 – 45 g dietary fibre daily),150mins/week of moderate physical activity (or 75mins/week of vigorous physical activity – or equivalent combination of both).

Importantly, the CALM lifestyle program does not have a weight loss goal, which is based on evidence demonstrating that associations between diet quality and depression are independent of body weight (e.g., [7, 56]). Moreover, shifting the emphasis (i.e. from a weight-focussed to a health-focused paradigm) is consistent with the Health at Every Size® movement [57], and believed to help reduce the pressure to lose weight, which can add another mental health burden and challenge [58].

While the CALM program is evidence-based and manualised to allow for replication, it also harnesses and is guided by peer-to-peer interaction and participant discussion, and is tailored to the specific needs of the group (e.g., motivation levels, confidence, skills, preferred learning styles, knowledge, health literacy). At each session, participants in collaboration with facilitators, are encouraged to set relevant goals for achieving positive lifestyle change. While the program focus primarily relates to nutrition and physical activity, participants may nominate other lifestyle targets that are critical to mental health (e.g., alcohol, smoking, substance use, sleep hygiene). Facilitators aim to develop rapport and a comfortable, respectful, sensitive and non-judgmental environment. All facilitators are highly skilled, with advanced training in motivational interviewing, health coaching, goal setting and mindfulness.

Example content and activities include: key foods and nutrients for mental health, nutrition recommendations for mental health, physical activity recommendations for general health and mental health and safety considerations (adapted from [6, 59]), creating healthy convenient meals and snacks, shopping lists, practical physical activity examples, physical activity ‘snacks’ [60], label reading, barriers and enablers to lifestyle changes, mindful eating, mindful physical activity, recipe modification and support groups. Additionally, at the start of each session, participants are provided with an opportunity to ask questions arising from or since the previous session, discuss their goals and homework. At the final session, goals achieved during the intervention period are discussed and summarised. Further, discussions include ways to stay motivated, maintaining changes and dealing with set-backs, with longer-term strategies developed to support sustainable changes, including sources for additional information and peer support.

To encourage engagement with healthful dietary habits, participants are sent a food hamper at completion of their first session, which contains the key components of the Mod*i*Med diet to inspire and promote dietary change. This strategy has previously been used to successfully promote engagement in RCTs of other Mediterranean-type dietary approaches [7, 61]. For the physical activity sessions, participants are provided with a resistance band as a convenient, portable, and effective alternative to free weights and weight machines. They are also sent a FitBit Charge 2 to self-monitor their physical activity (pedometer). Participants are also encouraged to complete a Mod*i*Med checklist, a physical activity tracker and utilise health apps, to increase their engagement and build on skills learnt throughout the sessions.

